**Fig. 6 Fig6:**
[figure not shown]
Examples of stimuli and correct judgments in the encoding and retrieval phase in Source memory task

### Psychological characteristics

Grit will be measured using the Japanese translation of the 8-items short Grit Scale [51]. This scale was originally developed in English by Duckworth and Quinn [52]. Participants will be asked to respond to each item (e.g., “I often set a goal but later choose to pursue a different one”) on a 5-point Likert scale, with higher scores indicating superior grit ability.

Resilience will be measured using the 6-item Brief Resilience Scale-Japanese version [53]. The scale was originally developed and validated in English by Smith and Dalen [54]. Participants will be instructed to respond to each item (e.g., “I tend to bounce back quickly after hard times”) on a 5-point Likert scale. A higher score indicates superior resilience.

Mindset will be measured using the Japanese version of the Self-Theories of Intelligence Scale [55], which is a modified version based on the theory of self-regulation by Dweck and Yeager [56]. Within this framework, mindsets are categorized into two distinct types: fixed and growth mindsets. Individuals with a fixed mindset believe that intelligence is innate and immutable, whereas those with a growth mindset perceive intelligence as something that can be developed through continuous effort. Participants in this study will be asked to respond to scale items using a 5-point Likert scale, with higher scores indicating a stronger inclination toward a growth mindset. This scale measures the degree to which individuals agree with statements reflecting the flexibility and malleability of their intelligence.

### Physical activity

The Global Physical Activity Questionnaire (GPAQ) will be used to assess physical activity during a typical week [57]. The GPAQ categorizes physical activity into three domains: work-related, transport-related, and leisure or recreational. This questionnaire quantifies physical activity in terms of Metabolic Equivalent Tasks (METs). Moderate-intensity activities are equivalent to 4 METs, while vigorous-intensity activities correspond to 8 METs. Based on these assessments, the GPAQ classifies physical activity levels into three categories (low, moderate, and high) to provide a comprehensive overview of an individual’s physical activity profile.

### Mood

Mood will be assessed using the Profile of Mood States (POMS) 2nd edition [58]. The POMS enables the measurement of Tension-Anxiety, Depression-Dejection, Anger-Hostility, Vigor-Activity, Fatigue-Inertia, Confusion-Bewilderment, and Friendliness. Participants will be instructed to respond to each item on a 5-point Likert scale.

### Constipation

Constipation Assessment Scale will be used to assess changes in bowel habits [59]. The self-assessment questionnaire consists of eight items rated on a 3-point Likert scale. Higher scores indicate a tendency for constipation.

### Sleep

The sleep state will be assessed using the Japanese version of the Pittsburgh Sleep Quality Index (PSQI) [60]. This scale was originally developed by [61]. The self-report questionnaire comprises 10 question categories based on sleep quality, sleep latency, sleep duration, habitual sleep efficiency, sleep disturbances, use of sleeping medication, and daytime dysfunction. A higher PSQI score indicates severe sleep problems.

### Quality of life (QOL)

This study will use the MOS Short-Form 36-Item Health Survey to assess health status in terms of both physical and mental dimensions [62]. This will enable a comprehensive assessment of participants’ health status by assessing their physical function, role-physical, bodily pain, general health perception, validity, social functioning, role-emotional, and mental health. The physical component comprises physical functioning, physical role, bodily pain, and general health perceptions, whereas the mental component includes vitality, social functioning, emotional role, and mental health. The results of these assessments are indicative of the QOL and offer insights into how individuals perceive and experience their health status.

### Mental health

Perceived stress will be measured using the 10-item Japanese version of the Perceived Stress Scale [63]. The scale was developed and validated by Cohen, Kamarck [64]. Participants will need to respond to each item, scored from 0 to 4. Higher scores indicate a greater degree of perceived stress.

Depression levels will be assessed using the Japanese version of the 6-item Kessler Psychological Distress [65]. Participants will need to respond to each item, scored from 0 to 4 (e.g., 0 = all of the time and 4 = none of the time). Higher scores indicate a greater level of depression.

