◦ We will use structural equation modeling (SEM) or mediation models to test whether changes in specific proteins or gut microbiota mediate the relationship between the exercise intervention and improvements in cognitive function.◦ For instance, if SCFA-producing bacteria increase in the exercise group, we will examine whether these changes lead to alterations in SIRT/mTOR signaling, which subsequently improve cognitive performance.Psychological and physical assessments◦ Grit, Resilience, Mindset, Depression, Stress, Quality of Life, and physical function measures will be incorporated into SEM analysis to examine how these psychological factors may mediate exercise-induced cognitive improvements.

In our primary analysis, an LMM is conducted to examine cognitive performance, gut microbiota, and aging control factors. As a secondary analysis, we will perform a linear model analysis using the Elastic Net approach for omics analysis and SEM to further explore the relationships among exercise, protein expression, psychological characteristics, mental health, and Quality of Life (QOL). Specifically, we will employ SEM to examine both the direct effect of exercise on cognitive function and explore potential indirect (mediating) effects through grit and resilience measures. We will randomly assign participants into exercise vs. control groups in a 1:1 ratio, ensuring that baseline variability in gut microbiota, cytokines, and protein levels is minimized across groups. Specifically,Randomization will be used to minimize systematic bias in baseline cognitive function, microbial and proteomic profiles.Baseline adjustments:◦ We will apply a linear mixed model with random intercept for adjustment of baseline conditions. Since this study will employ a randomized study design, baseline differences may be attributed to chance. For example, randomized intervention studies used a linear mixed model for assessing the effects of exercise on cognitive function [70–72] without adjustment for baseline conditions

By combining randomization with rigorous statistical adjustment, we can isolate the effects of the exercise intervention on outcome changes and reduce confounding from individual differences in biomarker levels.

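### The K6 item anchors contradict the stated direction of the depression score; scored as written and read as stated, the depression results would carry the wrong sign

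*Protocol article*

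**What the plan says.** The Mental health section of the protocol article names the instrument: "Depression levels will be assessed using the Japanese version of the 6-item Kessler Psychological Distress". Each item takes a value from 0 to 4, with the example anchors "0 = all of the time and 4 = none of the time". The next sentence gives the direction of the score: "Higher scores indicate a greater level of depression". The same section describes the Perceived Stress Scale, also scored 0 to 4 per item, and gives only its direction: "Higher scores indicate a greater degree of perceived stress".

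The score is used in the analysis. The list of secondary (exploratory) analyses, printed below the heading Primary outcomes in the statistical methods, says "Grit, Resilience, Mindset, Depression, Stress, Quality of Life, and physical function measures will be incorporated into SEM analysis", with the aim of examining mediation of the cognitive benefit. The same part of the article assigns SEM, with a multigroup analysis, to psychological characteristics and mental health.

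The section on plans for assessment and collection of outcomes {18a} states that the article sets out how each scale is scored. The K6 scoring is therefore something the article undertakes to give, not a detail it leaves to another document.

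**The concern.** The K6 is named as a measure of psychological distress and is used here for depression. If an item asks how often a symptom occurs, giving the most frequent answer 0 and the least frequent answer 4 makes a high total mean little distress. The following sentence says the opposite. A programmer who follows the anchors and an author who follows the interpretation would together report the depression result backwards: a benefit of exercise would appear as harm, or harm as benefit. In the same model the K6 would also run against the stress scale, although both are described as higher meaning worse. Reversal leaves p-values unchanged, so the significance tests would not reveal the error.

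**Working it through.** **Inputs**
- Number of items: 6 (Mental health section).
- Item range: 0 to 4 (same section).
- Anchors: 0 for the most frequent answer, 4 for the least frequent (same section).
- Stated direction: higher is more depressed (same section).
- Assumption: the items ask about distress symptoms. The item wording is not in the article; this is inferred from the scale's name and its stated use for depression.

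The article gives no K6 total range or expected difference, so there is no stated figure to reproduce.

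**Step 1: range and reversal.** The maximum total is 6 × 4 = 24.

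| Participant | Total with the printed anchors | Total if higher means more depression |
|---|---|---|
| Distressed all of the time on all six items | 6 × 0 = 0 | 6 × 4 = 24 |
| Distressed none of the time on all six items | 6 × 4 = 24 | 6 × 0 = 0 |

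Each item x becomes 4 − x, so the total T becomes T* = 24 − T. The correlation between T and T* is exactly −1.

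**Step 2: effect on single quantities.** Write D for a difference in mean T between the exercise and control groups. With T*, the difference is (24 − mean in exercise) − (24 − mean in control) = −D. A covariance, correlation or regression coefficient with T at one end changes sign in the same way. Standard errors are unchanged, so each test statistic only changes sign and its two-sided p-value stays the same.

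**Step 3: effect on mediation.** Let a be the path from exercise to depression, b the path from depression to cognition given exercise, and c′ the direct effect. Replacing T by 24 − T gives:
- a* = −a
- b* = −b
- a*b* = (−a)(−b) = ab
- c′* = c′, since the constant 24 goes into the intercept

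The indirect effect through depression keeps its sign and size. An indirect path that ends in depression, such as exercise to microbiota to depression, has only one link touching T and does reverse.

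**Step 4: numerical illustration.** Data were simulated for 200,000 subjects. The effects were assumed and are not taken from the article: exercise lowers latent distress by 0.3, and cognition depends on exercise (+0.2) and on latent distress (−0.3). The fits were ordinary least squares.

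| Coding | a | b | ab | Direct effect |
|---|---|---|---|---|
| Higher = more distress | −1.18 | −0.065 | 0.077 | 0.219 |
| Printed anchors | +1.18 | +0.065 | 0.077 | 0.219 |

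The single paths flip; the product and the direct effect do not. The sizes depend on the assumed effects, but the pattern of signs follows from Step 3 whatever the effects are.

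**The case against.** The strongest reply is that this is a transposed example in a condensed article. The anchors stand in a parenthesis introduced as an example, while the intended direction is a full sentence. The form, data dictionary and scoring script are not shown, so nothing establishes that any score will be computed wrongly. This stands as a limit on the consequence: the wrong sign is conditional. It does not remove the contradiction, because the anchors offered as the example are the ones that conflict with the interpretation.

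A reader might also infer that the mediation result for cognition would be reversed, since depression is among the SEM variables considered as mediators. The algebra does not support this: both links flip and their product is unchanged.

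The reach is limited too. Cognition, gut microbiota and metabolites, and aging-related proteins are the primary outcomes and are analysed by linear mixed models; the K6 is not among them. Where the article spells out the SEM's indirect effects in its summary of the secondary analysis, it names only grit and resilience. A reversed K6 should also be noticeable, because the trial collects perceived stress, the depression subscale of the POMS and the mental health part of the SF-36, with which it would be expected to correlate in the unexpected direction. Recoding loses no information. These points support a low severity. They do not make the printed scoring rule usable.

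**Conclusion.** The anchors and the stated interpretation of the K6 contradict each other, and the article mentions no reversal that would reconcile them. The textual contradiction is certain, given only that the items ask about distress. The effect on results is conditional on two things together: items summed with the printed anchors, and the total read in the stated direction. In that case the reversal is complete (24 − T). It affects the group difference in depression, each single path to or from depression, indirect paths that end in depression, and the correlations of depression with stress, quality of life and other measures.

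Not affected are the indirect effect of exercise on cognition through depression, the direct effect, the primary outcomes and the sample size. It would go too far to say that the depression score will be wrong, or that the mediation conclusion for cognition changes sign. Severity is minor, confined to secondary and exploratory analyses.

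**What to change.** Make the two statements in the Mental health section agree. Either give anchors that match the interpretation (0 for none of the time up to 4 for all of the time, total 0 to 24, higher meaning greater depression), or keep the printed anchors and state that items are reverse-scored before summing. Before analysis, check that the form given to participants, the data dictionary and the scoring script follow the same rule. As a quick test on the data, confirm that the K6 total correlates positively with perceived stress.

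The cost is a one-line correction and a script check. The article reports the trial as already underway, but responses already collected can be recoded without loss, and no change to the design, sample size or primary analysis is needed.

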### Gut microbiota

Participants will be instructed to collect fecal samples at home using the Metabolokeeper® preservation solution (TechnoSuruga Laboratory, Shizuoka, Japan) before the pretest and after completing the intervention period. Each participant will be provided with a collection kit containing a sterile collection tube prefilled with 5 mL of Metabolokeeper. All fecal samples will be sent to Technosuruga Laboratory Co., Ltd. for analysis of gut microbiota composition. The sample using a microbiome analysis reveals α and β diversities, as well as levels of SCFAs. The analysis will involve extracting DNA from fecal samples using an amplicon sequencing method. The DNA will then be amplified by polymerase chain reaction (PCR). Subsequently, the V3-V4 region of the 16S ribosomal RNA (rRNA) region will be targeted for sequence analysis using the Illumina MiSeq system, and the data is processed using QIIME2 software [66]. The taxonomic assignment of representative sequences will be performed using the Greengenes database [66]. Additionally, a physicochemical analysis of the fecal samples will be performed to detect SCFAs based on the metabolism of dietary fibers and carbohydrates by the gut microbiota.

### Factors of aging control

The proteome analysis method to be employed in this study will allow for the quantitative measurement of proteins. This method utilizes a technology based on aptamers designed to exhibit specific affinity toward target molecular structures, thereby enabling the detection of various protein configurations. Proteomic analysis can measure approximately 1000 different types of proteins. The analysis in this study will primarily reveal the cytokines related to the immune system. Furthermore, we will focus on identifying key proteins relevant to our research, including mTOR and SIRT, which are recognized as factors involved in the control of aging. For this purpose, blood samples from the participants will be analyzed using proteomic analysis.

### Physical function

To assess physical function, this study will measure hand grip strength, the 5-m walk test, and single-leg support tests. Participants will be asked to stand up and sit down from a chair five times as quickly as possible. Hand grip strength is considered an indicator of health status [67, 68]. Muscle strength is a diagnostic criterion for sarcopenia, characterized by a decline in muscle mass and strength with age. Previous studies have shown that hand grip strength is correlated with cognitive function in older adults [69]. It has been suggested that a decline in hand grip strength may lead to cognitive impairments during aging. The time taken to complete the five repetitions will be recorded. The participants will also be instructed to walk a distance of 5 m at their maximum walking speed. The time required to cover the distance will be recorded. Single-leg support tests will be performed twice for each leg, with the eyes open and closed. The duration for which the participant can maintain the stance will be recorded, with a maximum duration of 60 s.

### Plans to promote participant retention and complete follow-up {18a}

The training menu records will be provided as feedback to each participant in the intervention group to encourage participation by highlighting their cumulative efforts. In cases where participants are unable to attend due to urgent matters or illness, the responsible researchers will coordinate alternative attendance dates via email or telephone. Furthermore, to enhance participant retention, reminder emails will be sent regularly to encourage participants to participate in the upcoming week’s class.

### Data management {19}

The collected data will be anonymized, and signed consent forms will be stored in a locked cabinet for 5 years following the completion of the study. Electronic data will be saved on a secure site, accessible only within the campus network, and stored on a high-capacity, password-protected hard drive. In the event of a participant dropping out, we will specify the reason and report it.

### Confidentiality {27}

Each participant will be assigned a unique ID. The cross-reference table, linking names to ID codes, will be stored securely on campus without permission to be removed. Electronic data, including personal information, will be locked using passwords. This personal information, capable of identifying individuals, will not be included in the database for statistical analysis or disclosed in any conference presentations or publications.

### Plans for collection, laboratory evaluation, and storage of biological specimens for genetic or molecular analysis in this trial/future use {33}

Participants will undergo blood sampling before and after the study. Approximately 10 ml of blood sample will be obtained. The collected samples will be analyzed for complete blood count, including red blood cell (RBC) count, hemoglobin (Hb), hematocrit (Hct), mean corpuscular volume (MCV), mean corpuscular hemoglobin (MCH), mean corpuscular hemoglobin concentration (MCHC), platelet count, and white blood cell count (WBC), as well as blood metabolites. These blood samples will also be used for omics analysis.

The blood used for proteome analysis will be processed using a centrifuge to separate serum and plasma. The serum will be discarded, and the plasma will be stored at − 80 °C in a secure, temperature-controlled environment at Tohoku University for a period of 5 years following the completion of the study. After 5 years, all stored plasma specimens will be systematically destroyed in accordance with institutional guidelines and relevant regulations to ensure the protection of participant confidentiality and data integrity. Fecal samples will be sent to TechnoSuruga Laboratory Co., Ltd. for comprehensive gut microbiome analysis. After the completion of the analysis, all fecal specimens will be disposed of properly.

### Statistical methods

#### Statistical methods for primary and secondary outcomes {20a}

The statistical analyses will be performed using Python, R, Stata, and Mplus. The significance threshold for all statistical analyses will be set at *p* < 0.05. When the statistical analysis does not find statistical significance for our outcome based on our hypothesis, a 95% confidence interval will be used to estimate the effects of exercise. For cognitive performance, aging control factors, specific gut bacteria, and linear mixed model (LMM) analyses will be performed, including age and sex as covariates. The primary outcomes will be assessed as follows:

### Primary outcomes

Cognitive function◦ We will use the same standardized cognitive assessments outlined previously.◦ Analysis: LMM comparing changes in cognitive scores from baseline to 16 weeks after the intervention between the exercise and control groups, adjusting demographics (age and sex).Gut microbiota/metabolite◦ Measures: α- and β-diversity, relative abundance of key bacterial taxa, and SCFA concentrations.◦ Analysis: LMM for α and β-diversity/ metabolite (i.e., SCFA) changes from baseline to 16 weeks after the intervention. Baseline values will be included as covariates.Aging-related proteins◦ Targets: SIRT, mTOR, and other proteins relevant to aging control (aptamer-based detection).◦ Analysis: LMM to assess changes in protein expression levels from baseline to 16 weeks after the intervention, comparing intervention vs. control, with baseline adjustment.

As for the exploratory approach regarding gut microbiota and proteins in omics analysis, linear model analysis with the Elastic Net approach (e.g., the Lasso and Ridge approaches) will be used. This approach helps select the most appropriate regression model for the data. As for psychological characteristics and mental health, structural equation modeling (SEM) will be performed. Furthermore, in each group, a multigroup analysis will be conducted to reveal the effects of circuit training exercises on these psychological factors. The secondary (exploratory) outcomes will be assessed as follows:Comprehensive proteomics and cytokine analysis◦ We will apply an Elastic Net approach to ~ 1000 proteins to identify which markers show the largest change in response to the exercise intervention.◦ Markers identified by Elastic Net as differentially expressed will be further analyzed to determine their relationship with changes in cognitive function and gut microbiota measures.Mediation/path analysis (SEM)
◦ We will use structural equation modeling (SEM) or mediation models to test whether changes in specific proteins or gut microbiota mediate the relationship between the exercise intervention and improvements in cognitive function.◦ For instance, if SCFA-producing bacteria increase in the exercise group, we will examine whether these changes lead to alterations in SIRT/mTOR signaling, which subsequently improve cognitive performance.Psychological and physical assessments◦ Grit, Resilience, Mindset, Depression, Stress, Quality of Life, and physical function measures will be incorporated into SEM analysis to examine how these psychological factors may mediate exercise-induced cognitive improvements.

In our primary analysis, an LMM is conducted to examine cognitive performance, gut microbiota, and aging control factors. As a secondary analysis, we will perform a linear model analysis using the Elastic Net approach for omics analysis and SEM to further explore the relationships among exercise, protein expression, psychological characteristics, mental health, and Quality of Life (QOL). Specifically, we will employ SEM to examine both the direct effect of exercise on cognitive function and explore potential indirect (mediating) effects through grit and resilience measures. We will randomly assign participants into exercise vs. control groups in a 1:1 ratio, ensuring that baseline variability in gut microbiota, cytokines, and protein levels is minimized across groups. Specifically,Randomization will be used to minimize systematic bias in baseline cognitive function, microbial and proteomic profiles.Baseline adjustments:◦ We will apply a linear mixed model with random intercept for adjustment of baseline conditions. Since this study will employ a randomized study design, baseline differences may be attributed to chance. For example, randomized intervention studies used a linear mixed model for assessing the effects of exercise on cognitive function [70–72] without adjustment for baseline conditions

By combining randomization with rigorous statistical adjustment, we can isolate the effects of the exercise intervention on outcome changes and reduce confounding from individual differences in biomarker levels.

Although the trial is open-label, the data analyses will be conducted in a partially blinded manner. While participants and investigators will not be blinded due to the nature of the interventions, the statisticians will receive de-identified datasets with coded treatment assignments (e.g., “Treatment A” and “Treatment B”) to minimize potential bias. The treatment codes will only be revealed after the completion of the primary analyses.

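### Elastic Net selection among about 1000 proteins cannot show which are differentially expressed; its picks should be called candidates and an error-controlled comparison per protein added

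*Protocol article*

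**What the plan says.** All of this is in the Protocol article, Statistical methods {20a} and the Primary outcomes section under it.

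- The list is introduced as exploratory: "The secondary (exploratory) outcomes will be assessed as follows".
- The tool and its purpose: "We will apply an Elastic Net approach to ~ 1000 proteins to identify which markers show the largest change".
- The status given to what is selected: "Markers identified by Elastic Net as differentially expressed will be further analyzed". The next step relates these markers to the changes in cognition and gut microbiota.
- The same section then plans structural equation or mediation models to "test whether changes in specific proteins or gut microbiota mediate the relationship between the exercise intervention and improvements in cognitive function".
- One threshold covers everything: "The significance threshold for all statistical analyses will be set at *p* < 0.05".

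SIRT, mTOR and other named aging-related proteins are handled separately, by a linear mixed model comparing the arms with baseline adjustment. The Elastic Net step is the wider screen.

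**The concern.** The section gives Elastic Net an identification task that it cannot do. Elastic Net minimises squared prediction error plus a penalty, (1/2n)·‖y − Xb‖² + λ·[w·‖b‖₁ + (1 − w)/2·‖b‖²]. Protein j is kept only if its covariance with what the other selected proteins leave unexplained exceeds λ·w. Whether it is kept therefore depends on which correlated proteins are already in the model and on a penalty tuned for prediction. The size of that protein's own change between arms does not settle it. A non-zero coefficient has no p-value, no false discovery rate and no interpretation as a rank of change.

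Calling the kept proteins differentially expressed thus makes a claim about each protein that the method does not support. At stake is the protein list itself, which feeds the analyses of cognition and microbiota and could be published as a list of exercise-responsive proteins.

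**Working it through.** **Inputs from the Protocol article.** About 1000 proteins (Primary outcomes); evaluable N = 46, f = 0.25, power 0.9, α = 0.05 and 10% dropout (Sample size {14}); 1:1 allocation ({16a}), so 23 per arm. The Sample size section also gives 28 per arm against a total of 51; this does not affect the point.

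**The plan's own figure.** Take a repeated-measures ANOVA, group-by-time interaction, 2 groups, 2 times, with a correlation of 0.5 (assumed; not stated). Then λ_nc = f²·N·m/(1 − ρ) = 0.0625 × 46 × 2/0.5 = 11.5 on (1, 44) df. Power is 0.9125 at N = 46 and 0.8997 at N = 44, so 46 is reproduced. 46/0.9 = 51.1, which agrees with about 51. This effect equals a standardised difference in change scores of d = 1.0, since 1.0 × √(23/2) = 3.39 and 3.39² = 11.5.

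**Simulation assumptions.** The article does not fix the response variable, tuning, correlation or number of true changers. Both set-ups use 23 + 23 women and 1000 protein changes, with arm regressed on proteins and mixing 0.5.

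*Set-up A:* 10-fold cross-validation, 60 runs per scenario. The false share is averaged over runs that selected anything.

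| Truly changed | d | Within-block correlation | Runs selecting none | False share |
|---|---|---|---|---|
| 0 | – | 0 or 0.4 | 24 to 30 of 60 | 100% |
| 10 | 0.5 | 0 | 15 | 86% |
| 10 | 0.8 | 0 | 0 | 75% |
| 10 | 1.2 | 0 | 0 | 68% |
| 20 | 0.5 | 0.4 | 10 | 79% |
| 50 | 0.5 | 0 | 3 | 65% |
| 50 | 0.8 | 0 | 0 | 51% |

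With nothing changed, 50% to 60% of runs select at least one protein.

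*Set-up B:* 20 blocks with correlation 0.5, 5-fold cross-validation, 20 proteins truly changed by 1 SD. Ranges are over repeated runs.

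| Placement and penalty | Selected | True | False share |
|---|---|---|---|
| One block, CV minimum | 24.6 to 26.6 | 6.0 to 6.1 | 75% to 77% |
| Scattered, CV minimum | 33.6 to 34.6 | 12.9 to 13.0 | 61% to 63% |
| Scattered, one-standard-error penalty | 19.7 | 11.4 | (19.7 − 11.4)/19.7 = 42% |

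With nothing changed, 41% to 53% of trials select at least one protein. All 20 true proteins change by the same amount, yet about 6 are kept in one arrangement and about 13 in the other. So the selection is not a ranking of change. Benjamini–Hochberg at 5% on protein-by-protein tests finds about 7 true proteins in both arrangements, with 0.4 to 0.6 false.

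**Second step.** In set-up A, falsely selected proteins were tested against a cognitive change unrelated to them given arm. They reached p < 0.05 in 6% to 9% of cases when exercise improves cognition (d = 0.5), in 5% when it does not, and in 3% to 5% with arm adjusted for. A further run gave 7% to 11%. The same reasoning applies to microbiota measures, which were not simulated separately.

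**Re-testing the arm difference.** Re-tested for arm in the same women, falsely selected proteins reached p < 0.05 in 55% to 77% of cases (set-up A) and in 85% to 93% (set-up B, nothing changed), instead of 5%.

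**What error control can deliver.** With 20 scattered changers, Benjamini–Hochberg at 5% finds on average 0.16 true proteins at d = 0.5 (an empty list in 85% of trials) and 1.9 at d = 0.8 (empty in 33%).

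**The case against.** Three points on the other side carry weight.

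1. The analysis is labelled exploratory, and the proteins named in the hypotheses have their own baseline-adjusted models. This limits the harm. It does not make a penalised selection into a finding of differential expression.

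2. Elastic Net can be the more sensitive screen. With scattered changers it recovers about 13 true proteins against about 7 for Benjamini–Hochberg, and at 0.5 SD the latter finds almost nothing. A reader might infer that Elastic Net should be dropped in favour of false-discovery testing because it finds fewer true proteins. That holds only if the true changers sit in one correlated block, and the article gives no such structure. Replacing the screen is a trade-off; adding the error-controlled comparison is not.

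3. The penalty rule, resampling and stability checks are commonly left to an analysis plan, which is not at hand. Their absence is not criticised here. The point is the meaning that the article itself assigns to selection.

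A reader might also infer that the second step is circular, because the markers are tested in the women used to choose them. The high rates of 55% to 93% come from re-testing the arm difference. The article instead relates the markers to cognition and microbiota, where the inflation is small. Circularity remains if the arm effect is re-estimated for selected proteins, or if they enter the mediation models, where the exercise-to-protein path is that same arm difference.

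**Conclusion.** The rule is wrong as written. Elastic Net selection is presented as showing "identify which markers show the largest change in response to the exercise intervention" and as differential expression, and it shows neither. At 23 per arm the false share was about 50% to 86% with 10 to 50 true changers at the cross-validation minimum, and 42% in the one case run with a stricter penalty. With no true change, roughly 40% to 60% of trials still produce a list. The figures rest on assumed effects, correlation, tuning and choice of response. It would therefore go too far to say that the plan must yield mostly false markers: the share falls with many strong changers or a stricter penalty, and the article fixes neither. The later tests against cognition and microbiota are affected only slightly. Severity is minor to moderate.

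**What to change.** - Keep Elastic Net as an exploratory multivariable predictor. Call its selections candidates and report how often each protein is selected under resampling.
- Add one baseline-adjusted model per protein (arm effect, with age as covariate; sex is constant in this trial) with Benjamini–Hochberg control at 5%. Use the term differentially expressed only for proteins that pass. This extends to the whole panel the kind of model already planned for SIRT and mTOR.
- Where selected proteins enter mediation models, repeat the selection inside the resampling loop, or report those results as hypothesis-generating.

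The cost is a little more analysis, with no new samples or visits. The error-controlled list may be short or empty at moderate effects (about 0.2 true proteins on average at 0.5 SD in the simulation). The candidate list with selection frequencies still serves discovery in that case.
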